### Design and setting

ACT HIV is a parallel group, randomised (1:1), double blind, placebo-controlled multi-centre Phase III trial, comparing dexamethasone versus placebo for 6–8 weeks in addition to standard anti-tuberculosis and antiretroviral treatment. The trial will be set in two hospitals in Ho Chi Minh City, Vietnam and two hospitals in Jakarta, Indonesia. The trial will enrol 520 HIV-infected adults (≥ 18 years old) admitted to participating hospitals with a suspected diagnosis of TBM, as judged by the attending physician, and requiring immediate anti-tuberculosis treatment. Doctors making the diagnosis of TBM will all be senior physicians specialising in either infectious diseases or tuberculosis and lung diseases. All will receive additional diagnostic training and follow a diagnostic standard operating procedure. This trial schema is shown in
Figure 1.

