### Randomisation

Randomisation to ACT HIV will be stratified by participating hospital/site and modified MRC TBM severity grade. The randomisation list will be computer-generated based on random permuted blocks with variable block size following Oxford University Clinical Research Unit (OUCRU) standard operating procedures. A 24h web-based randomisation service will be provided. The OUCRU biostatistician in charge of randomisation list preparation will set up statistical code to generate the randomisation list and transfer it to the Study Pharmacist. The Study Pharmacist will then change the random seed, i.e. the initialisation of the random numbers generator, in the statistical code in order to blind the biostatistician and then run the code to prepare the final randomisation list. The generated randomisation lists will be securely incorporated within the trial database. A reliable manual back-up system will also be available. Randomisation to the three strategies for DILI will be 1:1:1 with stratification by initial randomisation (dexamethasone or placebo) and site. Authorised individuals will receive an allocated treatment strategy by visiting the same website used for the primary randomisation.

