### Primary endpoint analysis – ACT HIV (main trial)

The primary endpoint of the main trial is overall survival, i.e. time from randomisation to death, during 12 months of follow-up. Overall survival will be analysed with a Cox proportional hazards regression model with treatment as the only co-variate and stratification by TBM MRC severity grade at enrolment (I, II, or III) and country (Vietnam or Indonesia). The primary effect measure is the resulting hazard ratio comparing dexamethasone vs. placebo with a corresponding two-sided 95% confidence interval and p-value. The significance level of the associated two-sided test will be set to 5%. Kaplan-Meier plots and explicit survival estimates at 3, 6, 9, and 12 months of follow-up will also be calculated for the full populations and in the subgroups defined by TBM disease severity and country separately. The proportional hazards assumption will be formally tested based on scaled Schoenfeld residuals and visually assessed by a plot of the scaled Schoenfeld residuals versus transformed time. In case of a significant test, a formal comparison of the absolute risk of death at 12 months between the two groups will also be performed (using a Wald-type test based on Kaplan-Meier estimates at 12 months and associated standard errors using Greenwood’s formula).

The homogeneity of the treatment effect on overall survival across subgroups will be assessed by subgroup analyses and formal tests of interaction between treatment and the following grouping variables: TBM MRC severity grade at enrolment (I, II, or III), country (Vietnam or Indonesia), drug resistance pattern (MDR-TB or rifampicin mono-resistance, isoniazid resistant non-MDR, no or other resistance), ART status at enrolment (ART naive, ≤3 months of ART, >3 months of ART), and CD4 cell count at enrolment. To obtain an adjusted treatment effect estimate and to assess the effect of other covariates on survival, the primary endpoint will also be modelled using a multivariable Cox proportional hazards regression model including the following covariates (in addition to the treatment group): TBM MRC severity grade at enrolment, country, drug resistance pattern, ART status and CD4 cell count at enrolment. Multiple imputation will be used to handle missing covariates.

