### Primary endpoint analysis – DILI strategy study

For the analysis of the primary endpoint of the DILI strategy study, the non-parametric Wilcoxon rank sum test will be used for pairwise comparisons. An additional adjusted analysis (with adjustment for the initial randomisation, HIV-status, and the time from initial randomisation to the second randomisation) will be also be performed treating the outcome as an ordinal outcome and using a proportional odds logistic regression model (which can be interpreted as an extension of the Wilcoxon rank sum test). 

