### Secondary endpoint analysis

For ACT HIV, neurological disability (assessed by modified Rankin scale) at 12 months will be compared between the two arms with a proportional odds logistic regression model with the treatment assignment as the main covariate and adjustment for TBM MRC severity grade, and country. The result will be summarised as a cumulative odds ratio with corresponding 95% CI and p‐value. Patients with a missing 12-month disability assessment will be excluded from the main analysis but an alternative analysis based on multiple imputation (including disability assessments at earlier time points in the imputation model) will also be performed. Secondary time-to-event endpoints (time to neurological event or death, time to new AIDS event or death) will be analysed in the same way as the primary endpoint. The number of IRIS and HIV-associated malignancy events in each group will be summarised and the event rate calculated in each arm. Comparisons of the rates between the treatment arms will be based on a cause-specific proportional hazards model of the time to the first IRIS event (or HIV-associated malignancy, respectively) or death with treatment as the only covariate.

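### Randomisation is stratified by hospital and MRC grade, but the primary Cox model is stratified by country and grade: the test stays valid, with a modest efficiency cost only if same-country hospitals differ about two-fold or more

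*Protocol article*

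**What the plan says.** Main trial, section Randomisation: "Randomisation to ACT HIV will be stratified by participating hospital/site and modified MRC TBM severity grade". Section Design and setting places the trial in "two hospitals in Ho Chi Minh City, Vietnam and two hospitals in Jakarta, Indonesia", so there are four hospital strata crossed with three grades.

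Section Primary endpoint analysis – ACT HIV: a Cox model with treatment as its one covariate and "stratification by TBM MRC severity grade at enrolment (I, II, or III) and country (Vietnam or Indonesia". The multivariable Cox model in the same section also uses country, as does the Rankin model in Secondary endpoint analysis. Time to neurological event or death, and time to new AIDS event or death, follow the primary method. For IRIS and malignancy, the cause-specific model is of time to first event "or death with treatment as the only covariate", and no strata are stated.

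DILI study, section Randomisation: "Randomisation to the three strategies for DILI will be 1:1:1 with stratification by initial randomisation (dexamethasone or placebo) and site". Section Primary endpoint analysis – DILI strategy study: "the non-parametric Wilcoxon rank sum test will be used for pairwise comparisons", followed by an additional proportional odds model "with adjustment for the initial randomisation, HIV-status, and the time from initial randomisation to the second randomisation". Site is not in that list.

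**The concern.** The usual principle is to analyse by the factors used to randomise. Here MRC grade is carried over in full, but hospital only in the coarser form of country. No stated model contains hospital, so no planned analysis would show whether it matters.

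A prognostic factor left out of a Cox model pulls the hazard ratio towards 1. When allocation was balanced on that factor, the model-based standard error is also slightly too large. Both effects cost power, and the design has little to spare: it is sized at 80% for 229 deaths.

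Differences between hospitals in one country are plausible. Section Imaging gives serial brain MRI to participants at one Ho Chi Minh City hospital and leaves the other sites to routine care. Section Anti-retroviral therapy notes that routine practice on ART timing differs between centres. Neither says that mortality differs.

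**Working it through.** **1. The plan's own figure** (section Sample size justification – ACT HIV: hazard ratio 0.69, mortality 52% versus 40%, power 80%, two-sided 5%, loss to follow-up 5%).

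- Schoenfeld, 1:1: deaths = 4 × (1.960 + 0.842)² / (ln 0.69)² = 31.40 / 0.1377 = 228.02, rounded up to 229. This reproduces the stated number.
- Power with 229 deaths: (√229 / 2) × 0.3711 − 1.960 = 0.848, giving 80.2%.
- Participants: 229 / 0.46 = 498. Allowing for 5% loss, 498 / 0.95 = 525, or 498 × 1.05 = 523. The stated 520 is close.

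The sample size does not depend on the choice of strata.

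**2. Number of strata.** As planned: 2 countries × 3 grades = 6 strata, averaging 229 / 6 = 38 deaths. By hospital: 4 × 3 = 12 strata, averaging 229 / 12 = 19 deaths.

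**3. Effect of merging hospitals.** Simulation of 1,500 trials per scenario: 520 participants, permuted blocks within hospital × grade, control 12-month mortality 52%, 5% loss to follow-up. Both models were fitted to the same simulated trials.

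Assumed, because the documents do not give them:
- hospital shares 35/35/15/15%
- grade mix 35/40/25%
- grade hazard ratios 1/1.8/3.5
- country hazard ratio 1.5
- hazard ratio between the two hospitals of a country, varied from 1 to 3

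Each cell shows country × grade strata (as planned) / hospital × grade strata.

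| Same-country hospital hazard ratio | Estimated HR (true 0.69) | Power | Type I error (true HR 1) |
|---|---|---|---|
| 1.0 | 0.690 / 0.690 | 79.3% / 78.7% | 5.3% / 5.0% |
| 1.25 | 0.688 / 0.687 | 80.1% / 79.9% | 5.3% / 4.9% |
| 1.5 | 0.694 / 0.690 | 79.7% / 79.7% | 4.1% / 4.5% |
| 2 | 0.699 / 0.689 | 78.4% / 80.7% | 4.3% / 5.4% |
| 3 | 0.714 / 0.690 | 75.0% / 80.1% | 3.6% / 5.9% |

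The Monte Carlo standard error is about 1 point for power (√(0.8 × 0.2 / 1,500)) and 0.6 points for type I error. The 5.9% is therefore about 1.6 standard errors above 5%.

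**4. No strata at all** (the form of the IRIS and malignancy models, shown here on survival): HR 0.709 to 0.728, power 71% to 76%, type I error 2.5% to 3.7%. Most of this comes from leaving out grade. With no hospital difference, stratifying by grade alone moves the HR from 0.709 to 0.693 and power from 74.4% to 78.5%. The protocol gives no expected numbers of IRIS or malignancy events, so these figures do not carry over directly.

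**5. DILI.** The study is powered on ACT HIV and LAST ACT combined, about 100 + 70 = 170 participants, and time dead counts in the endpoint. In the earlier dexamethasone trial described under Use of adjunctive dexamethasone, HIV-infected deaths were 27/44 and 37/54. Subtracting from the totals leaves (87 − 27)/(274 − 44) = 60/230 (26%) and (112 − 37)/(271 − 54) = 75/217 (35%) among the others, against 61.4% and 68.5%. HIV status, which here identifies the trial, can thus be expected to be prognostic for the DILI endpoint. The earlier HIV-infected patients received no ART, so the contrast may now be smaller.

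**The case against.** A reader might infer that country strata bias the primary result or undermine its test. The documents do not support that. Randomisation within hospital and grade prevents confounding by hospital. Any attenuation is non-collapsibility of the hazard ratio, meaning a less conditional effect measure, and the simulated type I error of the planned model lies between 3.6% and 5.3%.

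A reader might also infer that hospital differences do dilute the hazard ratio. That is not shown. Country and grade are already strata, so only a residual difference between two hospitals in the same city, within grade, can act, and no hospital-level mortality is given. The planned multivariable Cox model also covers part of the measured case mix (drug resistance, ART status, CD4 count). All of this stands and limits the point to efficiency and consistency. Against it, the article fixes the strata outright, so this is not a detail left to the statistical analysis plan.

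For DILI, a Wilcoxon test has no hazard ratio to dilute. The plain test matches the one used in its power simulation, and the additional model already adjusts for initial arm and HIV status. Only a gain in efficiency remains. For IRIS and malignancy, twelve strata cannot be justified without event counts.

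**Conclusion.** The mismatch is plain on the page; its consequence is small and conditional. The planned primary test is valid and at worst conservative. The loss is negligible up to a 1.5-fold same-country hospital difference. At 2-fold, power falls by 80.7 − 78.4 = 2.3 points. At 3-fold it falls by 80.1 − 75.0 = 5.1 points, with the log hazard ratio attenuated by about 9% (ln 0.714 / ln 0.69 = 0.91). If hospitals do not differ, hospital strata cost 79.3 − 78.7 = 0.6 points, within simulation error. These sizes rest on the assumed hospital shares, grade mix and prognostic effects listed above. The case for changing is the asymmetry: almost nothing to lose, and a few points of power protected if hospitals differ strongly.

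**What to change.** Before unblinding:

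- Stratify the primary Cox model by hospital and MRC grade. Do the same for time to neurological event or death and time to new AIDS event or death. Keep country as a subgroup variable.
- If country strata are preferred, state the reason and add a hospital-stratified sensitivity analysis.
- Lesser point: stratify the IRIS and malignancy models at least by MRC grade, as far as event numbers allow.
- Lesser point: consider a van Elteren (stratified Wilcoxon) test by trial/HIV status and initial arm for the two primary DILI comparisons. This still leaves out site, which is a DILI randomisation factor ("with stratification by initial randomisation (dexamethasone or placebo) and site"), so say whether site is omitted to avoid thin strata.

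The cost is wording only, because the randomisation factors are already recorded. Neither the 229 deaths nor the 520 participants changes.

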### Primary endpoint analysis – DILI strategy study

For the analysis of the primary endpoint of the DILI strategy study, the non-parametric Wilcoxon rank sum test will be used for pairwise comparisons. An additional adjusted analysis (with adjustment for the initial randomisation, HIV-status, and the time from initial randomisation to the second randomisation) will be also be performed treating the outcome as an ordinal outcome and using a proportional odds logistic regression model (which can be interpreted as an extension of the Wilcoxon rank sum test). 

### Secondary endpoint analysis

For ACT HIV, neurological disability (assessed by modified Rankin scale) at 12 months will be compared between the two arms with a proportional odds logistic regression model with the treatment assignment as the main covariate and adjustment for TBM MRC severity grade, and country. The result will be summarised as a cumulative odds ratio with corresponding 95% CI and p‐value. Patients with a missing 12-month disability assessment will be excluded from the main analysis but an alternative analysis based on multiple imputation (including disability assessments at earlier time points in the imputation model) will also be performed. Secondary time-to-event endpoints (time to neurological event or death, time to new AIDS event or death) will be analysed in the same way as the primary endpoint. The number of IRIS and HIV-associated malignancy events in each group will be summarised and the event rate calculated in each arm. Comparisons of the rates between the treatment arms will be based on a cause-specific proportional hazards model of the time to the first IRIS event (or HIV-associated malignancy, respectively) or death with treatment as the only covariate.

### Analysis of adverse events

The number of patients with any adverse events and specific events, respectively, will be summarised and informally compared between the two treatment arms based on Fisher’s exact test. The total number of adverse event episodes per patient will also be summarised and informally compared based on a quasi-Poisson regression model with treatment as the only covariate. The following subgroups of adverse events will also be separately summarised: grade 3&4 adverse events; serious adverse events; serious adverse events possibly, probably, or definitely related to the study drug; adverse events leading to TB treatment or ART interruptions. Grade 3&4 laboratory abnormalities will be summarised in the same way as clinical adverse events.

Adverse events due to DILI will be recorded for the DILI study but also for the primary intervention (dexamethasone or placebo). An increased number of adverse events in DILI arms 1 and 2 are not expected, but if they do occur these adverse events will be associated with both the DILI randomisation strategy and for the primary intervention arm in which they occurred.

#### Analysis of ancillary studies

Ancillary studies will be analysed within the same groups as allocated based on the dexamethasone intervention. Allocation to the intervention (dexamethasone or placebo) is important for each sub study, given the effect of corticosteroids on inflammatory pathways, diabetes control, Strongyloides infection, raised intracranial pressure and adrenal suppression. DILI study patients will be analysed in their DILI arm, but an additional adjusted analysis (with adjustment for the initial randomisation) will also be performed.

### Baseline descriptive analyses

Baseline characteristics will be summarised as median (lower and upper quartiles) for continuous data and frequency (percentage) for categorical data. The amount of missing data for each baseline characteristic will also be displayed. 

## Ethical considerations

### Treatment

All participants will receive the best available treatment of tuberculosis and HIV, following local and national guidelines. Corticosteroids are commonly prescribed drugs and there is widespread experience and expertise concerning their safe use. The choice (dexamethasone), dose, route of administration and duration of study treatment follows the international guidance for the treatment of HIV-uninfected participants with TBM. Previous trials have demonstrated the safety of this or similar regimens. In particular, adjunctive corticosteroids were not associated with increased gastro-intestinal bleeding in a meta-analysis of all published TBM trials, although participants in this trial will be carefully monitored for this event. There is a possibility dexamethasone may increase the risk of HIV-associated malignancies, which will also be monitored closely in the trial.

### Confidentiality

Participants’ confidentiality will be maintained throughout the trial. Participants will be assigned a trial identification number and this will be used on case report forms (CRFs); participants will not be identified by their name. The investigator will keep securely a participant trial register showing identification numbers, surnames and date of birth. The unique trial number will identify all laboratory specimens, case record forms, and other records and no names will be used, in order to maintain confidentiality. Data submitted to OUCRU CTU and samples sent to central testing facilities will be identified only by the trial number and participant initials.

### Consent

Written informed consent must be obtained in order to enter into the trial and be randomised. If a participant lacks capacity, written consent must be obtained from a person with responsibility (e.g. family member/relative), in their own language before enrolment by the site PI or an appropriately trained doctor. All potential participants (or their families) will be given a participant information sheet clearly listing the risks and benefits of the trial. All potential participants (or their families) will be able to discuss participation with their consulting doctor who will be able to address questions not covered or arising from the participant information sheet. Incapacitated adults with TBM will be eligible to enter the trial. These adults have more severe disease and therefore may benefit most from adjunctive dexamethasone. We anticipate around 70% of participants with TBM will lack capacity at the start of treatment. An option will be given to patients to enrol in the main study, but not the DILI strategy study.

If consent is provided by a relative, the participant should be consulted and consent recorded if and when they have the capacity to do so. If they are happy to remain in the trial, the participant should complete a participant consent form at this time. If they wish to withdraw from the trial, no further trial-related procedures will be performed, but data to this point would be used in analysis. Data from any participant who dies before regaining capacity (but whose family member has provided consent) will be included in analysis.

### Protocol violations

All deviations from protocol will be addressed in source documents and reported to the OUCRU CTU.

### Withdrawing from the trial

A participant (or their relative) is free to refuse to participate in or withdraw from all or any aspect of the trial, at any time and for any reason. If a participant chooses to discontinue their trial treatment they should always be followed up (providing they are willing) and they should be encouraged not to leave the whole trial. If they do not wish to remain on trial follow-up however, their decision must be respected and the participant will be withdrawn from the trial. Participants may change their minds about stopping trial follow-up at any time and re-consent to participation in the trial.

### Data collection and storage

Clinical data and clinical laboratory data will be entered into CliRes, a 21 CFR Part 11-compliant data capture system provided by the OUCRU IT department. The data system includes password protection and internal quality checks, such as automatic range checks, to identify data that appear inconsistent, incomplete, or inaccurate. Trial data will be recorded onto paper CRFs and entered into CliRes. The participants will be identified by a unique trial specific number and/or code in any database. The name and any other identifying detail will not be included in any trial data electronic file. CRFs, clinical notes and administrative documentation will be kept in a secure location and held for 15 years after the end of the trial. Clinical information will not be released without written permission, except as necessary for monitoring, auditing and inspection purposes. Electronic data will be kept for at least 20 years at the OUCRU CTU.

### SPIRIT checklist

A SPIRIT checklist for this trial protocol is attached (
Supplementary File 5).

### Trial Committees

A Trial Management Group (TMG) will be formed to conduct the day-to-day management of the trial at the OUCRU CTU. This will include the CI, Head of OUCRU CTU, Trial Statistician, Clinical Project Manager, Trial Manager, Data Manager and Jakarta trial coordinator. The group will meet at least once per month, although may meet more or less often as required. The TSC has membership from the TMG plus independent members ([name] (Infectious Diseases Physician and Clinical Trialist, National University of Singapore, Singapore), [name] (Senior Tuberculosis Researcher and Trialist, University of Sydney, Australia), [name] [name] (Infectious Diseases Physician, Paediatric Hospital Number 1, Ho Chi Minh City, Vietnam)), including the Chair ([name] (Honorary Professor and Director Wellcome Centre for Infectious Diseases Research in Africa, University of Cape Town, South Africa)). The role of the TSC is to provide overall supervision for the trial and provide advice through its independent chair. The ultimate decision for the continuation of the trial lies with the TSC. The DMC ([name] (DMC Chair, Senior Statistician and Clinical Trialist, MRC Clinical Trials Unit, University College London), [name] (Senior Infectious Diseases/HIV Physician, University of Cape Town, South Africa) and [name] (Senior TBM Clinician and Researcher, Universitas Padjadjaran, Bandung, Indonesia)), will advise the TSC and can recommend premature closure or reporting of the trial, or that recruitment be discontinued or modified. The DMC is independent from the sponsor. Access to interim data and results will be confidential and strictly limited to the DMC and results (except for the recommendation) will not be communicated to the outside and/or clinical investigators involved in the trial. This trial is sponsored by The University of Oxford (Contact: University of Oxford, Research Services, [name], [contact]).

